### Study regimens

#### In participants susceptible to fluoroquinolones

RR-TB patients susceptible to fluoroquinolones are identified with the Xpert MTB/XDR assay (Cepheid; Sunnyvale, CA, USA). Experimental arms are seven five-drug oral regimens composed of agents selected from the following: bedaquiline, linezolid, a fluoroquinolone (moxifloxacin or levofloxacin), cycloserine, clofazimine and pyrazinamide. Composition of the regimens are described in Table 1. All regimens contain pyrazinamide except for regimen A1 and regimen B-SOC. To minimize potential toxicity, each regimen includes no more than two major QT-prolonging drugs (bedaquiline, clofazimine and moxifloxacin). Treatment duration of the experimental arms is 9 months. A 2-month extension of treatment is allowed with the presence of cavities at month 9 or in case of a positive culture at month 2. Baseline molecular drug susceptibility test (DST) of pyrazinamide will be performed using the whole gene sequencing (WGS) technique. The result of pyrazinamide molecular DST will be interpreted by technical staff at central laboratory of Huashan Hospital, Fudan University according to criteria published previously [9, 10]. Once a participant is proved resistant to pyrazinamide by WGS results obtained at baseline, pyrazinamide will be discontinued with no need for extra drug replacement.

The control regimen for fluroquinolone-susceptible participants is the current SOC regimen recommended by the national guidelines [11]. The SOC regimen comprises 1–2 drugs from group A (bedaquiline, linezolid, moxifloxacin or levofloxacin) and a drug from group B (clofazimine, cycloserine) along with ethambutol, pyrazinamide and high-dose isoniazid. Composition of the study regimen and dosing is described respectively in Tables 1 and 2. Treatment duration is 9 months in total, including a 4-month intensive phase and a 5-month continuation phase. The intensive phase could be extended to 5 months or 6 months if smear conversion has not occurred by month 4 or month 5.

**Table 1 Tab1:** Description of trial regimens

Group		Regimen	Duration (month)	Status
FQ(s)^a^	A-SOC	4 Bdq (Lzd) + Lfx (Mfx) + Cfz (Cs) + Pto + E + H_h_ + Z/5Lfx (Mfx) + Cfz (Cs) + E + Z	9	Recruiting
	A1	Bdq + Lfx (Mfx) + Lzd + Cs + Cfz	9	Recruiting
	A2a	Bdq + Mfx (Lfx) + Lzd + Cs + Z	9	Recruiting
	A2b	Bdq + Mfx (Lfx) + Lzd^b^ (2 months) + Cs + Z	9	Closed following protocol amendment

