	A2c	Bdq + Mfx (Lfx) + Lzd^c^ + Cs + Z	9	Closed following protocol amendment
	A3	Bdq + Lfx (Mfx) + Lzd + Cfz + Z	9	Recruiting
	A4	Bdq + Lfx (Mfx) + Cfz + Cs + Z	9	Recruiting
	A5	Mfx (Lfx) + Lzd + Cfz + Cs + Z	9	Closed following protocol amendment
FQ(r)	B-SOC	6Bdq + Lzd + Cs + Cfz /14Lzd + Cs +Cfz	20	Enrolment completed
	B1	Bdq + Lzd + Cs + Cfz + Z	9	Enrolment completed

Abbreviations: Bdq, bedaquiline; Cfz, clofazimine; Cs, cycloserine; Lzd, linezolid; Mfx, moxifloxacin; Lfx, levofloxacin; Z, pyrazinamide; H_h_, high-dose isoniazid; E, ethambutol; Pto, prothionamide; FQ(s), fluroquinolones susceptible; FQ(r), fluroquinolones resistant

^a^ Drug susceptibility of fluroquinolones is determined with Xpert MTB/XDR

^b^ Treatment duration of linezolid is 2 months in regimen A2b

^c^ Treatment duration of linezolid is 9 months and dose of linezolid is halved after 2 months in regimen A2c

**Table 2 Tab2:** Regimen drug doses by weight bands and usage

Drug	Weight band (kg)		Usage
	30–50 kg (mg/d)	> 50 kg (mg/d)	
Bedaquiline	400 mg daily for 2 weeks and then 200 mg three times a week		With meal
Linezolid ^a^	600 mg		Once daily, before or after meal
Moxifloxacin	400 mg		Once daily, before or after meal
Levofloxacin	500 mg	750 mg	Once daily, before or after meal
Clofazimine	100 mg		Once daily, before or after meal
Cycloserine	500 mg	750 mg	Once or divided in two doses, before or after meal
Pyrazinamide	1500 mg		Once daily, before or after meal
Prothionamide	500 mg	750 mg	Once or divided in two doses, before or after meal
Ethambutol	750 mg	1000 mg	Once daily, before or after meal
Isoniazid	400 mg	600 mg	Once daily, before or after meal

^a^ In regimen A2b, treatment dosage and duration of linezolid is 600 mg for 2 months. In regimen A2c, linezolid is routinely modified to 300 mg daily after 2 months of treatment and remains the same dose in subsequent treatment

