**Unfavourable outcome**: (1) At least one of the last two cultures (taken from respiratory samples collected on separate visits at least 7 days apart) is positive and laboratory cross contamination is ruled out. The latest between month 21 and month 23. (2) There is no culture result collected between month 21 and 23 or the result is positive due to laboratory cross contamination; and - bacteriological, radiological and clinical evaluation is unfavourable. OR - the most recent culture result is positive in the absence of laboratory cross contamination. (3) There is no culture result collected between month 21 and 23 or the result is positive due to laboratory cross contamination; and - either there is no other post-baseline culture result, or the penultimate culture result is positive due to laboratory cross contamination. OR - bacteriological, radiological and clinical evaluation is not available. (4) The last culture result (from a respiratory sample collected between month 21 and 23) is negative; and either there is no other post-baseline culture result, or the penultimate culture result is positive due to laboratory cross contamination; and bacteriological, radiological and clinical evaluation is unfavourable. (5) The last culture result (from a respiratory sample collected between month 21 and 23) is negative; and either there is no other post-baseline culture result, or the penultimate culture result is positive due to laboratory cross contamination; and bacteriological, radiological and clinical evaluation is not available. (6) Participant whose treatment regimen needed to be terminated or permanently changed ^a^ to a new regimen. (7) Treatment extension that does not meet protocol-defined extension criteria. (8) Initiation of a new RR-TB treatment regimen after the end of the allocated study regimen and before month 21 (relapse). (9) Loss to follow-up ^b^. (10) Death from any cause.

^a^ A permanent regimen change is constituted by any of the following: [1] adding or replacing two or more drugs in the allocated regimen; [2] adding second-line injectables in the allocated regimen; [3] replacing a group C drug with a group B drug (clofazimine, cycloserine) not originally included; [4] replacing a group B drug with a group A drug (moxifloxacin, levofloxacin, linezolid, bedaquiline) not originally included

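### Table 4, footnote a, omits single replacement of a group C drug by a group A drug, so a direct pyrazinamide-to-linezolid swap turns A4 into A1 and can still count as an A4 success

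*Protocol article*

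**What the plan says.** Unfavourable item (6) in Table 4 (Outcome measurements) is: "Participant whose treatment regimen needed to be terminated or permanently changed". Footnote a defines the permanent change by four alternatives:

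- The first sets a threshold on the number of drugs: "1] adding or replacing two or more drugs in the allocated regimen".
- Item [2] covers the addition of an injectable second-line drug.
- The third is a one-drug step up from C to B: "3] replacing a group C drug with a group B drug (clofazimine, cycloserine) not originally included".
- The last is a one-drug step up from B to A: "4] replacing a group B drug with a group A drug (moxifloxacin, levofloxacin, linezolid, bedaquiline) not originally included".

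A participant not already classified as unfavourable who meets the culture criteria is favourable.

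Table 1 gives A4 as "Bdq + Lfx (Mfx) + Cfz + Cs + Z" and A1 as "Bdq + Lfx (Mfx) + Lzd + Cs + Cfz". These two regimens differ by one drug: A4 has pyrazinamide where A1 has linezolid.

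For participants with pyrazinamide resistance on baseline sequencing, the section on fluoroquinolone-susceptible participants says that "pyrazinamide will be discontinued with no need for extra drug replacement". The Discussion adds that drug modifications are allowed after safety events or treatment failure.

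**The concern.** Items [3] and [4] follow a tier logic: replacing one drug by a drug of the next higher group is treated as a change of regimen. The step that crosses both tiers, from C to A, is missing. The list therefore scores the smaller upgrades as unfavourable and passes over the largest one.

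This matters because each open experimental arm in group A is one drug away from another. A4 is the only open experimental arm without linezolid. If a participant allocated to A4 takes linezolid in place of pyrazinamide and is scored as an A4 success, that result describes A1. The definition feeds the primary non-inferiority test of an open-label trial.

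**Working it through.** **1. Drug groups.** Group A is bedaquiline, linezolid and moxifloxacin or levofloxacin; group B is clofazimine and cycloserine (Study regimens; footnote a). The article does not itemise group C. Pyrazinamide (Z) is in neither list and is taken as group C by inference.

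**2. One-drug replacements checked against footnote a.**

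| Allocated | Out | In | Resulting drugs | Item met | Scoring |
|---|---|---|---|---|---|
| A4 | Z (C) | Lzd (A) | A1 | none | can be favourable |
| A2a | Z (C) | Cfz (B) | A1 | [3] | unfavourable |
| A3 | Z (C) | Cs (B) | A1 | [3] | unfavourable |
| A4 | Cfz (B) | Lzd (A) | A2a | [4] | unfavourable |
| A4 | Cs (B) | Lzd (A) | A3 | [4] | unfavourable |

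The same end regimen, A1, is scored differently by starting arm. Within A4, bringing in linezolid is scored differently according to which drug leaves.

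**3. Could another Table 4 item catch the A4 swap?** Item (7) concerns treatment extension. Item (8) concerns a new regimen after the allocated one has ended. The termination limb of item (6) does not clearly cover exchange of one drug. So no other item clearly does.

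**4. Stop first, add later.** If pyrazinamide is stopped and one oral drug is then recorded as an addition, items [3] and [4] (replacements) are not met, item [1] needs two drugs, and item [2] concerns injectables only. On that record A4, A2a and A3 all escape. For A2a and A3, scoring then depends on whether the switch is recorded as a replacement or as a stop followed by an addition.

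**5. Control arm.** In Table 1, A-SOC contains four drugs outside groups A and B (prothionamide, ethambutol, high-dose isoniazid, pyrazinamide); A4 contains one. On the same inference, replacing any of the four by a group A drug not in the participant's regimen is equally unlisted.

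**6. Size.** First, the plan's own figure, with control 0.70, experimental 0.80, margin 0.10, one-sided 2.5% and 80% power:

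n = (1.960 + 0.842)² × (0.70×0.30 + 0.80×0.20) / (0.80 − 0.70 + 0.10)² = 72.6, so 73 per arm, as stated.

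Next, place A4 at the margin (0.60 against 0.70) when switched participants count as unfavourable, and reclassify k of them as favourable. Each moves the arm's proportion by 1/73 = 1.4 points. With SE = √[pₜ(1−pₜ)/73 + p_c(1−p_c)/73],

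P(declare non-inferiority) = Φ[(pₜ − p_c + 0.10)/SE − 1.960].

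Example, k = 2 in A4 only: pₜ = 0.60 + 2/73 = 0.627; SE = 0.0780; (0.627 − 0.70 + 0.10)/0.0780 = 0.351; Φ(0.351 − 1.960) = 5.4%.

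| k | A4 only | both arms | A-SOC only |
|---|---|---|---|
| 0 | 2.5% | 2.5% | 2.5% |
| 2 | 5.4% | 2.5% | 1.0% |
| 3 | 7.6% | 2.5% | 0.6% |
| 4 | 10.5% | 2.5% | 0.4% |
| 5 | 14.2% | 2.5% | 0.2% |

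The documents give no count for k in any arm; 0 to 5 is an assumption.

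**The case against.** Several counter-arguments carry weight.

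- **The contrast between arms is narrower than it looks.** It holds only for a direct one-for-one swap of pyrazinamide. If pyrazinamide is stopped and a drug is later recorded as added, A4, A2a and A3 are scored alike. This stands.
- **Direction.** A reader might infer that the gap helps A4 pass. Every arm is tested against A-SOC, which has more drugs through which the gap can act, so the documents do not support a net direction.
- **Size.** A reader might take 5% to 14% as the true error rate. Those figures reclassify A4 alone, with assumed counts; the other two columns of the table show no change or a fall.
- **Frequency.** A reader might infer that the pyrazinamide place is often open. The article gives no resistance frequency and says that no replacement is needed.
- **Single additions.** A reader might want every single group A or B addition scored as unfavourable. Tolerating one added drug is a visible threshold in item [1] of a pragmatic trial. Such a rule could hardly apply to A1, which already has every group A class and both group B drugs, but would bear heavily on A-SOC. Lowering only the control rate makes non-inferiority easier to declare: on the assumptions above, 2 to 5 control participants moved to unfavourable give 5.3% to 13.4%. It is a different endpoint, not the correction of an error.
- **Group C is inferred.** If pyrazinamide were not group C, item [3] would not catch the A2a and A3 swaps and the contrast between arms would go. The A4 swap would still be unlisted.

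None of this explains why C to B and B to A count while C to A does not. The definition is printed as a list of qualifying changes, so this is not detail left to a fuller document.

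**Conclusion.** The point holds in a limited form. Footnote a contradicts its own tier logic by omitting the C-to-A step. With pyrazinamide taken as group C, a direct pyrazinamide-to-linezolid swap in A4 yields A1 and can be scored as an A4 success, whereas the direct swaps to A1 from A2a and A3 are unfavourable.

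The net effect on the comparison with A-SOC is unknown in direction and size. The rise from 2.5% to about 5% to 14% for 2 to 5 participants is an upper illustration. It needs A4 to be truly at the margin, 73 evaluable per arm, the gap acting in A4 only, and a count that the documents do not give.

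A reader might also infer that a planned comparison of A4 with A2a or A3 is compromised. The statistical section tests each experimental arm against control only, so that is not supported.

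**What to change.** Reconcile items [3] and [4] of footnote a so that replacing a group C drug by a group A drug not originally in the regimen is scored in the same way as the C-to-B and B-to-A replacements, identically in all arms including A-SOC. State which drugs form group C. State also whether stopping pyrazinamide and then adding one drug is scored as a replacement, so that the outcome does not depend on how the switch was entered. No rule making all single group A or B additions unfavourable is required.

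Decide this before analysis, by people blind to outcome by arm, and document it as an amendment. It changes outcome scoring only, not which drug changes are permitted in care.

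Cost: a short edit to Table 4 and re-derivation of the outcome from regimen data already recorded. The downside is a few more unfavourable outcomes, some of them in A-SOC, and an amendment to the primary endpoint definition while fluoroquinolone-susceptible participants are still being recruited.

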#### Eligibility criteria

Participants eligible for the INSPIRE TB study must fulfil all inclusion criteria:

Male or female participants aged 16–75 years old, with weight over 30 kg, regardless of HIV status.Pulmonary TB with rifampicin resistance diagnosed with either phenotype DST (obtained within 60 days prior to randomisation) or World Health Organization (WHO)-approved rapid molecular diagnostic testing [12].Signed informed consent form (ICF).

Participants will be excluded from the trial if they meet any of the following criteria:

Participants with known allergies, hypersensitivity, or contraindication to any of the study drugs as described in the Supplementary material.Participants with central nervous system TB, tuberculous osteomyelitis and arthritis, or hematogenous disseminated pulmonary TB.Participants known to be pregnant or breastfeeding at the time of enrolment.Participants who have received second-line anti-TB drugs for more than 14 days prior to randomisation, including bedaquiline, moxifloxacin, levofloxacin, linezolid, cycloserine and clofazimine.Participants in critical condition and with a physician-estimated survival of less than 3 months.

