#### Follow-up duration and participant timeline

The baseline visit includes collection of medical history, a physical examination, evaluation of symptoms and signs, laboratory tests, a 12-lead electrocardiogram, visual acuity assessment, assessment for peripheral neuropathy, smear, culture, and the Xpert MTB/XDR assay. During the treatment period, follow-up visits are scheduled monthly until treatment completion. After treatment, visits are conducted every three months in the first six months, and then every six months until 21 months after randomisation. Additional visits could be conducted as clinically needed. Follow-up assessment during treatment and post-treatment assessment are shown in Table 3. MTB strains are collected and sent to the central lab for whole genome sequencing at baseline and post-baseline visits as needed.

**Table 3 Tab3:** Schedule of enrolment, interventions, and assessments

	Baseline	Treatment Period						Post-treatment Period		
		monthly						M12	M15	EOS^#^
Timepoint (month)	-2 weeks to M0	M1	M2	M3		…	EOT^**^			
Inform consent	**×**									
Eligibility assessment	**×** ^*****^									
Treatment allocation	**×**									
Susceptibility testing for rifampicin	**×**									
Rapid molecular test for FQ resistance	**×**									
Treatment adherence assessment		**×**	**×**	**×**		**×**	**×**			
Evaluation of signs and symptoms	**×**	**×**	**×**	**×**		**×**	**×**	**×**		**×**
Sputum Tests (smear and culture)	**×**	**×**	**×**	**×**		**×**	**×**	**×**		**×**
Electrocardiogram	**×**	**×**	**×**	**×**		**×**	**×**	if indicated		
Routine blood tests and chemistry	**×**	**×**	**×**	**×**		**×**	**×**	if indicated		
Chest Radiography	**×**	if indicated			**×**			if indicated		
Haemoglobin A1c	**×**	Every three months in participants with diabetes								
TSH, FT3, FT4	**×**	monthly if on prothionamide								
HIV test, hepatitis B and C	**×**									
Pregnancy test	**×**									
Visual acuity assessment	**×**	if indicated						if indicated		
Assessment for peripheral neuropathy	**×**	if indicated						if indicated		
SDS and SAS	**×**	if indicated						if indicated		

Abbreviation: EOT: end of treatment; EOS: end of study; TSH: thyroid-stimulating hormone; FT3: free triiodothyronine; FT4: free thyroxine; SDS: self-rating depression scale; SAS: self-rating anxiety scale

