^b^ Loss to follow-up is defined in case that a participant fails to complete two or more consecutive scheduled visits and cannot be reached after at least three phone calls and one home interview

Main secondary outcomes are measured in fluoroquinolone-susceptible and fluoroquinolone-resistant arms respectively. Secondary outcomes are defined as follows:

Time to sputum smear conversion in the mITT population.Time to sputum culture conversion in the mITT population.The proportion of participants with a favourable outcome at 21 months post-randomisation in the per-protocol (PP) population.The proportion of participants with grade 3 or higher adverse event (AEs), serious adverse events (SAEs) at 21 months post-randomisation in the safety population.All-cause mortality and treatment relevant mortality at 21 months post-randomisation in the safety population.The proportion of participants with treatment relevant SAEs at 21 months post-randomisation in the safety population.The proportion of participants with grade 3 or higher QTc prolongation in the safety population.The proportion of participants experiencing permanent drug discontinuation or replacement due to QTc prolongation in the safety population.

Exploratory outcome measures are defined as the following:

The proportion of participants with a favourable outcome at 21 months after randomisation in regimen A2a, A2b and A2c in the mITT population.The proportion of participants with grade 3 or higher myelosuppression, peripheral neuropathy and optic neuropathy in regimen A2a, A2b and A2c in the safety population.The proportion of participants with linezolid discontinuation or dose reduction due to AE in regimen A2a, A2b and A2c in the safety population.

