#### Statistical considerations and analysis population

Analysis populations included the intention-to-treat (ITT) population, the modified intention-to-treat population and the per-protocol population. The ITT population includes all participants undergoing randomisation. The mITT population is defined as participants who undergo randomisation and had a culture positive for *Mycobacterium tuberculosis* collected at baseline or within two weeks of randomisation, excluding those with baseline isolates susceptible to rifampicin based on phenotypic DST. Additionally, for the mITT analysis, participants in Group A with fluoroquinolone-resistant baseline isolates confirmed with phenotypic DST will be excluded. Conversely, those in Group B with fluoroquinolone-susceptible isolates will be excluded. Participants who undergo randomisation in error or do not receive any study treatment after randomisation are also excluded from the mITT population. The PP population is derived from the mITT population, excluding those with inadequate treatment, defined as having completed less than 80% of the prescribed doses within 120% of the planned duration. Participants who discontinue treatment due to treatment failure, adverse events, or death will not be excluded from the PP population. Safety analyses will be conducted in the safety population, which includes all participants who receive at least one dose of the study regimen, and will be analysed according to the treatment actually administered.

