The primary efficacy analysis will be conducted in the mITT population, and efficacy outcomes will be reported as supportive analyses from both the PP and ITT populations. The absolute between-group difference with 95% confidence interval (CI) in the proportion of participants with a favourable outcome will be calculated. The non-inferiority of an experimental arm versus the control arm will be established if the upper bound of the 95% CI is less than 10% (the margin of non-inferiority). In group A, multiple experimental arms are compared to the control regimen. Type I error rate will be controlled with a pre-planned fixed sequence method. First, the regimen with the highest expected treatment success rate will be compared to the control. If non-inferiority is established, comparisons will proceed sequentially to the next experimental regimen in descending order of expected efficacy. For any regimen that demonstrates non-inferiority, a subsequent test for superiority over the control will be performed.

Patient characteristics will be described with median and range (or interquartile range), or numbers and percentages. The median time to smear and culture conversion will be estimated in each arm using the Kaplan-Meier method and between-group difference will be compared with the log-rank test. Proportion of participants with any grade 3–5 adverse event, any serious adverse event (SAE) and any treatment-related SAE will be described with numbers and percentages.

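### Time to smear conversion is assigned to the whole mITT population, which is defined by culture, so participants who are smear-negative at baseline enter with no conversion to observe

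*Protocol article*

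**What the plan says.** Outcome measurements lists "Time to sputum smear conversion in the mITT population" first among eight secondary outcomes; time to culture conversion follows with the same population.

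Statistical considerations and analysis population defines mITT as randomised participants who "had a culture positive for *Mycobacterium tuberculosis* collected at baseline or within two weeks of randomisation", less those excluded on rifampicin or fluoroquinolone susceptibility testing. It adds: "Participants who undergo randomisation in error or do not receive any study treatment after randomisation are also excluded from the mITT population". None of these conditions refers to smear.

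Eligibility criteria admits "Pulmonary TB with rifampicin resistance diagnosed with either phenotype DST (obtained within 60 days prior to randomisation") or by an approved rapid molecular test. Smear positivity is not required there either.

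For the analysis, "The median time to smear and culture conversion will be estimated in each arm using the Kaplan-Meier method". Arms are then tested against each other by log-rank.

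Baseline smear is collected: the baseline visit in Follow-up duration and participant timeline includes "assessment for peripheral neuropathy, smear, culture, and the Xpert MTB/XDR assay", and Table 3 marks smear and culture at baseline and at each monthly treatment visit.

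**The concern.** A time-to-conversion analysis needs everyone in it to start in the unconverted state. For culture the mITT definition secures this, because a positive culture is the condition of entry. For smear it does not. A participant who is culture-positive and smear-negative at baseline meets the stated definition and has no event to wait for.

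Such participants carry no information about how fast a regimen clears smears, yet they shift the curve in a direction that depends on how they are scored. The reported median would then describe a mixture rather than conversion, would be hard to compare with other trials, and the between-arm test would be less sensitive. In an open-label trial it is also better not to leave the scoring to be settled once results can be seen.

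**Working it through.** **Inputs from the article.** 73 mITT participants per arm in group A and 82 in group B (Sample size assumptions); monthly visits on treatment; 9-month experimental regimens.

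**Check of the article's sample sizes.** n = (1.96 + 0.8416)² × [p₁(1−p₁) + p₂(1−p₂)] / (difference + margin)².
- Group A: 7.849 × (0.21 + 0.16) / 0.20² = 72.6, so 73.
- Group B: 7.849 × (0.2275 + 0.1875) / 0.20² = 81.4, so 82.

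Both match. They serve the primary outcome; the article states no figure for smear conversion.

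**Assumptions not in the documents.** Smear-negative share s of 20, 30, 40 or 50%; exponential conversion with a true median of 2 months among smear-positives; hazard ratio 1.6; censoring at month 9; two-sided 5% log-rank test.

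**Median on a continuous time scale.**
- Scored as converted at time 0: (1−s)·2^(−t/2) = 0.5, so t = 2·log₂[2(1−s)].
- Scored as never converting: s + (1−s)·2^(−t/2) = 0.5, so t = 2·log₂[(1−s)/(0.5−s)].

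| s | Smear-positives only | Converted at time 0 | Never converting |
|---|---|---|---|
| 20% | 2.0 | 1.4 | 2.8 |
| 30% | 2.0 | 1.0 | 3.6 |
| 40% | 2.0 | 0.5 | 5.2 |
| 50% | 2.0 | 0 | not reached |

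If they are instead scored as converted at the month-1 visit, the cumulative proportion at month 1 is s + (1−s)(1 − 2^(−1/2)) = 0.43, 0.51, 0.58 and 0.65. The visit-based median is then 2 months at s = 20% and 1 month at 30-50%. The values of 0.5 and 0 in the table belong to time-0 scoring only.

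**Log-rank power, 73 per arm.** Two separate simulations of 2,000 runs per setting; where two figures are given they are the two simulations.

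| s | Smear-positives only | Converted at month 1 | Converted at time 0 | Never converting |
|---|---|---|---|---|
| 20% | 70 / 69% | 63 / 66% | 56% | 22% |
| 30% | 63 / 62% | 55 / 56% | 46% | 14% |
| 40% | 57 / 56% | 48 / 47% | 37% | 10% |
| 50% | 47 / 48% | 36 / 38% | 30% | 7% |

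The month-1 loss is 7, 8, 9 and 11 points in the first simulation and 3, 6, 9 and 10 in the second: roughly 3-11. For time-0 scoring it is 69−56 = 13, 62−46 = 16, 56−37 = 19 and 48−30 = 18 points. For never converting it is 41-48 points.

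**Other inputs.** With a control median of 3 months, hazard ratio 1.7, s = 40% and 73 per arm (800 runs), power is 0.67 in smear-positives only, against 0.54 (month 1), 0.48 (time 0) and 0.17 (not converted by month 9). At 82 per arm the figures are 0.69, 0.58, 0.49 and 0.19.

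**Not at risk (censored at time 0).** Under the same alternative inputs at 73 per arm and s = 20, 40 and 50%, power is 0.79, 0.68 and 0.56, against 0.77, 0.67 and 0.56 with exclusion. The two agree within simulation error.

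**Type I error.** With no regimen effect, rejection is 4-6% under every scoring. In a run of 3,000 per setting it was 0.042-0.051 (month 1) and 0.046-0.056 (never converting).

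**Chance imbalance.** The SD of the between-arm difference in smear-negative share is √[2s(1−s)/73], which is 0.066 at 20% and 0.083 at 50%: 7-8 points.

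**The case against.** The strongest reply is that the harm depends on a scoring rule the article does not give. It does not define smear conversion in detail, and rules on events and risk sets for a secondary endpoint are commonly left to the full protocol or SAP. Conversion ordinarily means a change from positive to negative, so mITT could be read as the parent set, with smear-negatives simply not at risk; the check shows that this is harmless. That stands, and it limits the size of the point. It does not remove it: the article names an analysis set, the same one as for culture, and an SAP that restricted the analysis to smear-positives would depart from the outcome as stated.

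The never-converting scoring is also the least plausible. Under Study regimens, extension of the A-SOC intensive phase depends on smear conversion not having occurred, and it would be odd to place baseline smear-negatives there. The largest distortions should therefore not be taken as the expected ones.

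A reader might infer that chance imbalance in the smear-negative share would show up as a treatment effect, or that this share rather than the regimen would drive the result. That is not supported. Randomisation balances the share in expectation, and type I error stays near 5%. Imbalance adds noise, not systematic bias.

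A reader might also infer that these participants can only be scored as converted or as never converting. The not-at-risk option shows otherwise.

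**Conclusion.** The concern holds in a limited form. The stated population for time to smear conversion does not match the endpoint, and nothing in the eligibility criteria, the mITT definition or the analysis text corrects the mismatch. Unless smear-negatives are treated as not at risk, the median is displaced in a direction set by the scoring, and log-rank power falls by roughly 3-11 points under month-1 scoring and by more under the other two.

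The direction of the power loss does not depend on the particular assumptions tried; its size does. The smear-negative share, conversion rate and hazard ratio are all assumed. The outcome is one of eight secondary outcomes, with no power claim or decision rule attached. The primary non-inferiority analysis, its sample size and time to culture conversion are untouched. It should be corrected, but it does not threaten the trial's main conclusion.

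**What to change.** Define the outcome as time to sputum smear conversion among mITT participants who are smear-positive at baseline. Report per arm how many are included and how many mITT participants are smear-negative at baseline. Leave time to culture conversion in the full mITT population.

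This is one line in the protocol or SAP. Baseline smear is already collected, so no new data or visits are needed, and group A recruitment was still open at the article's last status date (September 2025), so the change can be made before database lock. The cost is a smaller n for this outcome. That costs no power relative to the whole-mITT analysis, because the participants removed carry no information on conversion.
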